## Methods and design

### Study design

This single center, prospective, rater-blind, three arm clinical trial will investigate the efficacy of a FE paradigm on motor and non-motor symptoms in individuals with PD. A total of 100 individuals with mild to moderate idiopathic PD will be enrolled. CYCLE Trial protocol is approved by the Cleveland Clinic Institutional Review Board and all participants will sign an informed consent prior to beginning the study. Written informed consent was obtained for any photographs that have been taken for publication. A schematic overview of the enrollment, testing, and intervention is shown in Figure 1.

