### Power analysis

For Aim 1, the UPDRS motor score will be the primary outcome. Our power analysis was calculated based on UPDRS motor data from our previous project comparing FE and VE interventions on UPDRS ratings. We observed a mean (95% confidence interval (CI)) reduction of -5.3 (-18.0, 7.4) in the FE group and 0.4 (-15.3, 16.1) in the VE group from baseline to end of treatment (EOT) at 8 weeks. This corresponds to a difference (improvement, reduction) in means (95% CI) of -4.9 (-20.6, 10.8), standard deviation (SD) of difference = 8.0, P = 0.004. Assuming similar variability for the current proposal, with N = 40 subjects per exercise group, we will be able to detect differences of 5.0 or more between groups on UPDRS with 90% power at the 0.05 significance level, adjusting for 3 group comparisons at each of EOT evaluations. No published data exists for outcomes in Aim 2 or 3 with respect to exercise and PD. In general, with 40 subjects per exercise group, power will be 99 percent to detect differences of 1.2 SDs or more between the groups. For Aims 1-2, comparisons at particular time points power is 90% to detect differences of 1.3 SD, applying a Bonferroni correction for analyzing time points (2 post-intervention times) individually. All calculations assume Tukey adjustment for comparing the 3 groups.

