### Randomization

Participants will be randomized 2:2:1 into FE, VE, or no-exercise control group. The uneven allocation of subjects was selected due to the promising results of the preliminary data by [name], et al. indicating there is a benefit to cardiovascular exercise that would not been seen in a control group [20,21]. Enrollment will total 18 weeks: two weeks allotted for baseline evaluations, 8 weeks of exercise intervention or control period, and 8 weeks for a follow up period in which the participant is instructed to return to their baseline level of physical activity.

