### Data analysis

Participants in all three groups will be compared descriptively on potentially confounding baseline variables (i.e., age, disease severity, and levodopa equivalent daily dose (LEDD)) to assess the extent of any imbalance across groups. Baseline variables in which there appears to be a clinically important baseline difference, or in which the standardized difference (absolute value of difference in means divided by pooled SD) between any 2 groups is greater than 10% will be included as covariates. P-values from these baseline variable comparisons will not be used to determine the need for covariate adjustment, as that criterion can be misleading.

The FE, VE, and the no-exercise control groups will be compared on each outcome of interest (motor, non-motor) using repeated measures analysis of covariance. For motor and non-motor outcomes, groups will be compared on outcomes at the mid-treatment, EOT, EOT + 4 weeks, and EOT + 8 weeks adjusting for the baseline (on and off medication) period as a covariate. The effects of group, time, and the group-by-time interaction will be assessed for each outcome. In the case of a significant interaction, the groups will be compared at each time point. Tukey’s correction for multiple comparisons will be used. Data will be transformed as needed to meet model assumptions. In addition to p-values, the estimated treatment effect and its 95% CI will be of interest as these data will aid in formulating exercise recommendations and potential benefits. For each hypothesis, significance level will be set at 0.05. Each participant’s change in fitness based on change in peak VO_2_ from CPX testing will be used as a covariate. This will remove the effect of possible differences in improvement in fitness level across the groups from confounding the results. Correlation between LEDD and the time spent within target HR zone during training, amount of work performed, and change in primary outcome variables in motor and non-motor outcomes will be assessed. If the LEDD is significantly correlated with these outcomes, it will be included as a covariate in the related analysis.

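### With exactly three groups, single-step Tukey is valid but needlessly conservative; a closed (step-down) version keeps the 5% family-wise error and adds some power, by an amount that depends on the control mean and the SD

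*Protocol article*

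**What the plan says.** The Data analysis section of the protocol article plans a repeated measures analysis of covariance of the forced exercise (FE), voluntary exercise (VE) and control groups. If the group-by-time interaction is significant, the groups are compared at each time point. For those comparisons, "Tukey’s correction for multiple comparisons will be used", and "For each hypothesis, significance level will be set at 0.05". The same section wants the estimated effect and its 95% confidence interval alongside the p-values.

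The Power analysis section makes the same choice: "All calculations assume Tukey adjustment for comparing the 3 groups". It claims that the trial can "detect differences of 5.0 or more between groups on UPDRS with 90% power at the 0.05 significance level", "with N = 40 subjects per exercise group", from a pilot "standard deviation (SD) of difference = 8.0, P = 0.004". For analyses of individual time points it adds a Bonferroni correction over two post-intervention times. No step-down or closed form of Tukey is named in either section.

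**The concern.** Single-step Tukey holds every pair to the critical value needed when all three groups are equal. With three groups that protection is more than is needed after the first rejection. If any two of the three pairwise nulls are true, the third is true as well, so once one pair is known to differ, at most one of the other two nulls can still hold. Testing what remains at the unadjusted level then cannot push the family-wise error above 5%.

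What is at stake is power for FE versus VE, the contrast on which the trial is sized. Some rejections that the design could support are given up, with no change in the guaranteed error rate.

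**Working it through.** **Inputs.** Difference 5.0, SD 8.0 and 40 per exercise arm (Power analysis). Total: "A total of 100 individuals with mild to moderate idiopathic PD will be enrolled" (Study design). Allocation: "Participants will be randomized 2:2:1 into FE, VE, or no-exercise control group" (Randomization), hence 40/40/20 and 100 − 3 = 97 residual degrees of freedom, ignoring covariates. Two-sided testing is assumed because sidedness is not stated, and 8.0 is taken as the within-group SD. No control mean is given, so it is varied.

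**The plan's own figure first.**
- Standard error for FE versus VE: 8.0 × √(1/40 + 1/40) = 1.789. Noncentrality: 5.0 / 1.789 = 2.795.
- Tukey critical value: q(0.95; 3, 97)/√2 = 3.366/1.414 = 2.380, a per-pair two-sided level of 0.019.
- Power (noncentral t, 97 df): 66%. The stated 90% does not reproduce. Under Tukey it would need an SD of about 6.1 or a difference of about 6.6.
- Unadjusted critical value 1.985: power 79%. This is the ceiling for any closed test of this pair.

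**Why the closed test is valid.** With three groups, every intersection of two or more pairwise nulls is the global null. Closed testing therefore needs only a 5% test of the global null (largest pairwise statistic against 2.380) and a 5% test of each pair. A pair that exceeds 2.380 opens the gate itself and also exceeds 1.985, so every single-step rejection is kept.

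**Power for FE versus VE at one outcome and time point** (400,000 simulated trials per scenario, alpha 0.05, SD 8.0, FE 5 points better than VE):

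| Assumed control mean | Single-step | Closed | Gain (points) |
|---|---|---|---|
| Midway between FE and VE | 66% | 67% | about 1 |
| Equal to VE | 66% | 71% | about 4.5 |
| 1 point worse than VE | 66% | 73% | about 7 |
| 2.5 points worse | 66% | 76% | about 10 |
| 5 points worse | 66% | 79% | about 13 |

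**Sensitivity.**
- SD about 6.1 (where single-step Tukey does reach 90%): 90% to 93% with control equal to VE, and 90% to 95% with control 5 points worse.
- Alpha 0.025 (Bonferroni over two times), SD 8.0: Tukey value 3.753/1.414 = 2.654, unadjusted value 2.277. Power goes from 56% to 60% with control equal to VE, and from 56% to 69% with control 5 points worse.

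**Family-wise error.** Under the global null both procedures reject in 5.0% of trials. With one true null pair and the third arm far away, the closed test is at 5.0% and single-step Tukey at 1.9%.

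**The case against.** Four points can be made on the other side.

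- **Tukey is a standard, valid choice, used consistently in both sections.** This stands. A reader might infer that the plan's test is wrong or its error rate uncontrolled; nothing in the documents supports that. It is also true that single-step is the usual reading of the text, not a stated detail.
- **Single-step Tukey comes with simultaneous intervals that agree with its decisions, and the step-down form has no simple equivalent.** This stands as a small cost. The Data analysis section asks for a 95% interval for the effect but does not ask for simultaneous ones.
- **The size of the gain rests on a control mean that is not given.** This stands and limits the claim. A reader might take 5 to 13 points as the general gain. The upper end needs control 5 points worse than VE. If the pilot VE change of 0.4 were repeated, control would have to worsen by about 0.4 + 5 = 5.4 points in 8 weeks, and the protocol reports no such decline. The Randomization section expects a benefit of exercise over control but gives no size. The pilot VE change, close to zero, sits nearer to the scenario with control equal to VE.
- **The SD of 8.0 is a pilot figure, and baseline adjustment may lower the residual SD.** This also stands. The documents do not say by how much, which is why the SD near 6 is shown.

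**Conclusion.** The point holds as an optional gain in efficiency. For one outcome at one time point, a Tukey-gated closed test keeps the 5% family-wise error, keeps every rejection of the single-step test and adds some. At difference 5, SD 8 and 40/40/20, FE versus VE power rises from about 66% to about 71% if control equals VE, and to about 79% if control is 5 points worse. It rises by only about 1 point if control lies midway between FE and VE, and by about 3 to 5 points at an SD near 6 with control equal to VE or worse.

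Two stronger inferences fail. The closed test does not restore the stated 90%, because at SD 8 it cannot exceed the 79% of the unadjusted test; the gap between 66% and 90% is a separate matter. Nor can the planned group-by-time interaction test act as the gate. It addresses whether group differences change over time, not whether the three groups are equal at a given time. The power figures above also leave out the chance that this interaction test stops the time-point comparisons from being reached.

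**What to change.** Add to the Data analysis section that, for each outcome and time point at which the groups are compared:

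- if the largest of the three pairwise statistics exceeds the Tukey critical value (about 2.38 at alpha 0.05, or the value for the Bonferroni-adjusted alpha where the time-point correction applies), the remaining pairs are tested at the unadjusted level of that same alpha;
- otherwise no pair is declared different;
- the gate is this three-group range test, and the group-by-time interaction test does not replace it.

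Report 95% confidence intervals for all three contrasts, labelled as unadjusted or Tukey-simultaneous, and note that they may disagree with the step-down decision in borderline cases.

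The cost is a few lines of text and that possible mismatch between interval and decision. No extra participants or data are needed.

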The *Cyc*lical *L*ower Extremity *E*xercise for Parkinson’s (CYCLE) Trial is designed to test the hypothesis that FE and VE, while both aerobic, produce different clinical outcomes as a result of differential effects on the CNS. Specifically, the aims of the CYCLE trial are: 1) To determine the effects of FE and VE on motor function in individuals with PD; 2) To determine the effects of FE and VE on non-motor function in individuals with PD; and 3) To determine the pattern of magnetic resonance imaging (MRI) activation associated with FE and VE. It is hypothesized that FE will elicit significantly greater improvements in clinical and biomechanical measures of motor and non-motor performance when compared to voluntary and no-exercise control groups. Further, it is hypothesized that FE will elicit increased cerebral blood flow and cortical and subcortical activation following exercise, while voluntary and no-exercise groups will result in no change in the pattern or extent of activation as seen on neuroimaging.

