### Cardiopulmonary exercise testing

Following completion of initial screening, participants will undergo cardiopulmonary exercise testing (CPX). CPX protocol is administered by an exercise physiologist from the preventative cardiology department of the Cleveland Clinic. Testing will be completed on a Lode cycle ergometer using MedGraphics CardiO_2_/CP system with Breeze software. The participant will be instructed to take his/her PD medication as prescribed on the day of testing. A 12-lead electrocardiogram will be assessed prior to exercise, continuously during exercise, and during exercise recovery. Participants will exercise at an initial load of 25 Watts, increasing by 25 Watts every two minutes until 100 Watts, and then increasing by 50 Watts every two minutes until the American College of Sports Medicine’s Guidelines for Exercise Testing criteria for test termination are reached [28]. The participant’s peak volume of oxygen uptake (VO_2_) will be calculated as the highest 30 second average of VO_2_ during the CPX test. A Cleveland Clinic cardiologist will interpret the results of the test, and those with normal responses to exercise will be randomized while those with abnormal responses will be advised for further medical work up.

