### Voluntary exercise intervention group

Subjects randomized into the VE group will participate in 3 weekly exercise sessions over the course of 8 weeks for a total of 24 sessions. Exercise sessions will consist of a 5-minute warm up, a 40-minute main exercise set, and a 5-minute cool down on a standard stationary bicycle. All sessions will be completed under the guidance of an exercise physiologist. For participants who are deconditioned upon study enrollment, rest breaks will be allowed for 2 minutes every 10 minutes during the 40-minute main exercise set. Participants will be asked to pedal at a self-selected pace, and will be encouraged to achieve their target HR range, which will be calculated from their resting and maximal HR during the CPX test using the Karvonen formula at 60-80% of their max exertion [29]. HR, cadence, and power will be recorded every 5 minutes, and the rate of perceived exertion will be recorded every 10 minutes. Supervising exercise trainers and study personnel will be certified in Basic Cardiac Life Support. If a participant exhibits signs of cardiac distress or hemodynamic compromise, the exercise session will be stopped immediately and the on-call physician will be paged to the exercise laboratory. Following completion of the 24 session exercise intervention, participants will be instructed to resume pre-enrollment activity levels.

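### The efficacy models adjust for change in peak VO2, a post-randomisation effect of the exercise, which alters the exercise-versus-control comparisons, and the FE–VE comparison if fitness gains differ

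*Protocol article*

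**What the plan says.** The Data analysis section compares FE, VE and no-exercise control on each motor and non-motor outcome "using repeated measures analysis of covariance". In the same paragraph it adds: "Each participant’s change in fitness based on change in peak VO_2_ from CPX testing will be used as a covariate". The reason given is: "This will remove the effect of possible differences in improvement in fitness level across the groups from confounding the results". No condition is attached. The adjusted model is not labelled as a sensitivity, mediation or exploratory analysis, and no analysis without the covariate is described.

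The first aim in the Background is "To determine the effects of FE and VE on motor function in individuals with PD", and the second is the same for non-motor function. The hypothesis is that "FE will elicit significantly greater improvements in clinical and biomechanical measures of motor and non-motor performance when compared to voluntary and no-exercise control groups". Neither is limited to effects that bypass fitness.

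**The concern.** A confounder of a treatment comparison has to influence both treatment and outcome. In a randomised trial nothing that happens after allocation can influence allocation. Change in peak VO2 is something the exercise is expected to produce, so it lies downstream of the assigned group.

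Entering it as a covariate does two things. It takes out whatever part of the benefit runs through improved fitness. It also compares people with equal fitness change across arms, who need not be alike in other respects: general health, adherence or disease course may drive both fitness gain and UPDRS change. The adjusted contrast then no longer has the protection of randomisation.

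At stake is whether the reported effects answer the stated aims, including the comparison with no exercise. The article also says that the estimates and their confidence intervals will help form exercise recommendations. An effect net of fitness gain does not serve that purpose.

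**Working it through.** **Place in the causal order.**
- The Cardiopulmonary exercise testing section says that "those with normal responses to exercise will be randomized". Baseline peak VO2 therefore precedes randomisation, and the change from it follows.
- Both exercise arms have 24 aerobic sessions, with a target heart rate set "using the Karvonen formula at 60-80% of their max exertion" in the VE arm and a matched dose in the FE arm. The No exercise control group section has controls keep their usual activity.
- Fitness gain is thus an expected result of assignment.

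**Inputs for an illustration.** The article gives no expected VO2 gain and no VO2–UPDRS slope, so there is no figure of its own to reproduce on this point.
- From the Power analysis section: SD = 8.0, taken here as the within-arm SD of the UPDRS motor outcome.
- Assumed: within-arm correlation r between VO2 change and UPDRS outcome of -0.2 to -0.4 (a larger fitness gain goes with a lower, better score).
- Assumed: VO2 gain in the exercise arm d = 0.5 to 1 within-arm SD above control.

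**Formula.** In a linear model at one time point, adjusted difference = unadjusted difference − slope × d. With VO2 change in SD units, slope = r × SD. The shift is therefore −r × SD × d, and a positive shift counts against exercise.

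| r | d = 0.5 | d = 1 |
|---|---|---|
| -0.2 | 0.2 × 8 × 0.5 = 0.8 | 0.2 × 8 × 1 = 1.6 |
| -0.3 | 0.3 × 8 × 0.5 = 1.2 | 0.3 × 8 × 1 = 2.4 |
| -0.4 | 0.4 × 8 × 0.5 = 1.6 | 0.4 × 8 × 1 = 3.2 |

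**FE versus VE.** The shift is −r × SD × (d for FE − d for VE). It is zero when the gains are equal and takes either sign when they are not.

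**Simulation of the mechanism.** There were 4,000 trials per row, with 40 FE, 40 VE and 20 control, within-group outcome SD 8 and VO2-change SD 1. All effects, gains and slopes are assumed. The model without the covariate recovered the assumed total effect to within 0.05 in every row. Each cell shows the total effect, then the estimate with the covariate.

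| Scenario | FE−control | VE−control | FE−VE |
|---|---|---|---|
| Gains of 1 SD in both arms, slope -2.5 (half of the FE effect through fitness) | -5.0 → -2.6 | -2.5 → 0.0 | -2.5 → -2.5 |
| Gains of 1 SD in both arms, slope -5 (all through fitness) | -5.0 → 0.0 | -5.0 → 0.0 | 0.0 → 0.0 |
| FE gains 1 SD, VE 0.5 SD, slope -5 (all through fitness) | -5.0 → 0.0 | -2.5 → 0.0 | -2.5 → 0.0 |
| FE gains 0.5 SD, VE 1 SD, slope -2.5 | -5.0 → -3.8 | 0.0 → 2.5 | -5.0 → -6.3 |
| Fitness has no effect on outcome; shared cause; gains of 1 SD in both arms | -5.0 → -3.0 | -5.0 → -3.0 | 0.0 → 0.0 |
| No true effect; shared cause; FE gains 0.5 SD, VE 1 SD | 0.0 → 1.0 | 0.0 → 2.0 | 0.0 → -1.0 |

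In the last two rows the shared cause has correlation 0.5 with fitness gain and -0.5 with the UPDRS outcome. That gives r = 0.5 × (-0.5) = -0.25 and a shift of 0.25 × 8 × 1 = 2.0, which matches the formula. A slope of -5 implies r = -5/8 = -0.625, steeper than the range in the first table, so those rows show the limiting case. Tukey-adjusted power for FE−control falls from 48% to 12% in the first row and from 47% to 2% in the second.

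**The case against.** The best defence is that the trial wants to know whether FE works beyond fitness. The Background hypothesis is that the two modes, although both aerobic, act differently on the central nervous system. The arms are dose-matched, and if their fitness gains are equal the FE–VE contrast, which is the one the power calculation rests on, is unchanged on average. If no unmeasured factor drives both fitness gain and outcome, the adjusted result is a different estimand (the effect not acting through fitness) rather than a biased one.

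Much of this stands. The question is coherent, and for FE–VE harm does depend on unequal gains. But it is a mediation question. Ordinary adjustment answers it only if there is no unmeasured common cause of fitness change and outcome, and randomisation does not secure that. If gains are equal, the covariate is not needed for its stated purpose; the article itself allows for differences. In either case both control contrasts remain exposed.

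Two further inferences that a reader might draw are not supported:
- **Lost participants.** Table 1 lists no repeat exercise test, which might suggest that participants would lack the covariate and leave the model. But Table 1 omits the test at baseline too, where it is plainly scheduled, and a change in peak VO2 implies a second test. Its timing and the handling of missing values may sit in the full protocol.
- **Lost precision.** For 40 versus 20 with d = 1, imbalance alone multiplies the variance by (1/40 + 1/20 + 1/97)/(1/40 + 1/20) = 1.137. The covariate also cuts residual variance by the factor 1 − r². The net factor is 1.137 × 0.91 = 1.035 at r = -0.3 and 1.137 × 0.84 = 0.955 at r = -0.4, so there is no consistent loss.

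**Conclusion.** The point holds. The plan treats a consequence of assignment as a confounder and, as written, makes the fitness-adjusted model the only efficacy model. For FE−control and VE−control the estimate no longer targets the total effect named in the aims: it loses any benefit acting through fitness and is open to bias from shared causes.

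On the assumptions shown, the shift is 0.8 to 3.2 UPDRS motor points against exercise. This is an illustration; the document fixes neither the correlation nor the fitness gain.

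Three limits apply. A reader might infer that all three comparisons are biased, but FE–VE moves only if fitness gains differ between those arms, and then in either direction. A reader might infer that the shift is always towards the null, but that depends on the assumed sign of r, which shared causes could change. A reader might also measure the shift against the 5.0-point detectable difference, but the Power analysis section derives that from FE-versus-VE pilot data with 40 per exercise group and sets no separate target for exercise against 20 controls.

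**What to change.** - Make the model without change in peak VO2 the primary analysis for all motor and non-motor outcomes. Baseline peak VO2, measured before randomisation, may be a covariate.
- Report change in peak VO2 by arm as an outcome.
- Keep the fitness-adjusted model only as a labelled exploratory or mediation analysis, and state its assumption that no unmeasured common cause drives both fitness change and outcome.
- Remove the wording that describes differences in fitness gain as confounding.

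The cost is a rewrite of the covariate sentence and its rationale in the Data analysis section. No new data are needed, and the question of an FE effect beyond fitness can still be examined.
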